\* The maximum inspiratory mouth pressure (MIP) and maximum expiratory mouth pressure (MEP) were measured using a standard mouthpiece and a device (Vitaropower KH115, Chest MI Co. Ltd., Tokyo, Japan) according to American Thoracic Society/European Respiratory Society).

j. Inflammatory biomarkers: Interleukin-6 (IL-6), Tumor Necrosis Factor- $\alpha$  (TNF- $\alpha$ ), and High sensitivity CRP are measured.

The reason of the measurement: In recent years, it has been reported that COPD is a chronic systemic inflammatory disease and that systematic inflammation leads to worsening of COPD and causes comorbidities. On the other hand, it has been reported that acupuncture has an anti-inflammatory effect, and our previous study found some improvements in inflammation biomarkers related to COPD.

\*Evaluate the difference 12 weeks and one year (52 weeks) after the baseline.

k. Patients' expectations for acupuncture

Expectations for acupuncture were evaluated on the following Six-level Likert scale. Evaluation is performed at the time of baseline evaluation after informed consent (conducted before allocation).

"0: I have no expectations, 1: I do not expect much, 2: Indifferent, 3: I'm expecting a little, 4: Have medium expectations, 5: I have high expectations"

\*Patients' expectations for acupuncture are assessed at baseline only.

\*All evaluations are carried out by independent evaluators not involved in the research.

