#### • **Statistical Analysis**

1. Handling of cases and target group for analysis

In this study, cases enrolled in clinical trials and excluding dropouts will be the main analysis group.

2. Method of analysis

In this study, based on data analysis is performed by setting two analysis groups, FAS (Full Analyze Set) and PPS (Per Protocol Set).

FAS and PPS are defined as follows.

FAS: All assigned patients except for dropped out patients

PPS: Patients who achieved 40 or more acupuncture treatments in one year, excluding dropout patients.

Distributions of all the outcome measures at baseline are shown.

For the primary outcome measures, the secondary outcome measures, and other outcome measures, ratios or means of the differences between baseline and 12 weeks and between baseline and 52 weeks are calculated.

For all outcome measures, we look at the changes of variables in 12 weeks (from baseline to 12 weeks later) and in 52 weeks (from baseline to 52 weeks later). And then, for main outcome measure and secondary outcome measures, we compare these 12-week-change and 52-week-change using the analysis of covariance (ANCOVA) with baseline values and GOLD classification as covariates and treatment group as the factor of interest.

For the change from baseline in other outcome measures, an independent sample t-test is use.

Continuous variables and ordinal variables are shown as the means (standard deviation), and their significant differences are shown by 95% confidence intervals (CI) and p-values (significance level 0.05). Count variables are shown as the number of counts and percentages, and X2 test or Fisher's exact test results are shown with p-values (significance level 0.05).

For the changes in arterial blood oxygen saturation and in pulse during the 6-minute walk, we use the mixed effects model to analyze the difference between the 12-week-change and 52-week change. In this mixed effects model, the fixed effects are groups and times, the interaction terms are group x time, the intercept of random effects is individual, the slope is time, and the estimation method is the maximum likelihood method.

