Furthermore, COPD has been reported recently to be not just a respiratory disease but a systemic and progressive inflammatory disease. Especially, it has been reported that with the increase of inflammatory cytokines such as IL-6, IL-8, TNF- $\alpha$ , and TGF- $\beta$ , inflammation spreads not merely lung but systemically and occurs with comorbidities such as hypertension, diabetes and various cancers). Moreover, acupuncture stimulation has been reported recently such as in Nature Medicine to be effective in suppressing inflammatory cytokines such as IL-6, IL-8, TNF- $\alpha$ , and TGF- $\beta$ ). If inflammatory cytokines can be suppressed by acupuncture, acupuncture would be able to prevent not only the severity of COPD but also its comorbidities. Therefore, we consider that to perform research on acupuncture for COPD is highly significant and that the scientific rationality of this research has a sound basis.

As for the expected research results, the improvements of QOL and prognosis are possible. COPD causes deterioration of QoL due to dyspnea on exertion, the chief complaint, and COPD gets worse from disuse syndrome due to the decreased activity which then leads to the bedridden condition for a long period of time. Therefore, it is necessary to sustain and improve QoL of COPD patients by reducing and preventing dyspnea. COPD guideline does report that exacerbation of dyspnea and declining QoL are related to the patient's prognosis. Despite the indication of the guideline, many COPD patients are still deprived of

their daily lives and social activities due to dyspnea on exertion. We need to expand and compensate the current COPD treatment. We consider that the expected results from our study would improve conditions of dyspnea on exertion and QoL and contribute to improving the prognosis of COPD patients by utilizing acupuncture. COPD is also a systemic inflammatory disease, it is also expected that acupuncture would reduce inflammation. Since our research aims to expand the existing medical practice, we consider that our research could significantly contribute to the academics.

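### IL-6, TNF-α and hs-CRP are tied to an unadjusted t-test on raw change; if they are right-skewed, a log-scale ANCOVA has clearly more power (minor)

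*Protocol*

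**What the plan says.** The Protocol, section 6, Outcome Measures, C. Other outcome measures, item j, names IL-6 and TNF-α and closes its list with "High sensitivity CRP are measured". The item calls for the difference from baseline at 12 and 52 weeks. Its rationale is that "our previous study found some improvements in inflammation biomarkers related to COPD", and section 8 adds that "it is also expected that acupuncture would reduce inflammation". Neither place gives an effect size.

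The Statistical Analysis part of section 6 sets the method by outcome tier:

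- Primary and secondary outcomes are compared "using the analysis of covariance (ANCOVA) with baseline values and GOLD classification as covariates and treatment group as the factor of interest".
- Everything in the third tier, including item j, gets this rule: "For the change from baseline in other outcome measures, an independent sample t-test is use".
- The summary is common to all tiers: "Continuous variables and ordinal variables are shown as the means (standard deviation"), with "95% confidence intervals (CI) and p-values (significance level 0.05").

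No transformation, rank test or exception is stated for the markers. The text says that baseline distributions will be shown, but nothing in the analysis depends on what they look like.

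**The concern.** A serum concentration cannot fall below zero, and a treatment that suppresses it plausibly acts in proportion to its level. If so, raw change is largest in the patients with the highest values. They then supply most of the variance in a t-test, and the mean (SD) of change describes a typical patient poorly. Change without baseline adjustment also leaves in the noise that comes from each patient's starting level. With few patients per arm, averaging gives little protection against either.

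At stake is a mechanism claim that the protocol makes itself. A null marker result from an insensitive test could be read as evidence against an anti-inflammatory effect. This is a rule that the protocol states, not a detail left open for a later analysis plan.

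**Working it through.** **1. The plan's own sample size.** Inputs from section 6, Sample Size: SGRQ difference 10, SD 10.0, two-sided 0.05, power 0.8. The normal approximation gives n = 2(1.960 + 0.842)² × (10/10)² = 15.7, so 16 per arm. The exact two-sample t-test gives 16.71, rounded up to 17, with power 0.807. The stated 17 per arm is reproduced. It also equals (44 − 10)/2, the number left after the planned dropouts. The protocol gives no power figure for the markers.

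**2. Model for a marker (all assumed).** Baseline: log B = s·Z₁. Follow-up: log Y = s(ρZ₁ + √(1−ρ²)·Z₂), plus log(1−δ) in the acupuncture arm, with Z₁ and Z₂ independent standard normal. Log-scale SD s runs from 0.3 to 1.2, correlation ρ is 0.5 or 0.7, and reduction δ is 0, 30% or 50%. There are 17 per arm and 20,000 simulated trials per setting, so the Monte Carlo error is at most √(0.25/20,000) ≈ 0.35 points.

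**3. Analyses compared.**
- As planned: t-test on Y − B.
- Raw ANCOVA: Y − B on group and B.
- Log t-test: log Y − log B.
- Log ANCOVA: log Y on group and log B. GOLD class was not simulated.

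For example, at s = 0.8, ρ = 0.7 and a halving (log 2 = 0.693), the SD of log change is 0.8·√(2 × 0.3) = 0.620, a standardised effect of 1.12. The log ANCOVA residual SD is 0.8·√(1 − 0.49) = 0.571, a standardised effect of 1.21.

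**4. Power for a halving (%).**

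| s | ρ | Raw t (planned) | Raw ANCOVA | Log t | Log ANCOVA |
|---|---|---|---|---|---|
| 0.5 | 0.5 | 81 | 98 | 97 | 99 |
| 0.5 | 0.7 | 94 | 100 | 100 | 100 |
| 0.6 | 0.5 | 65 | 91 | 90 | 96 |
| 0.6 | 0.7 | 82 | 97 | 99 | 99 |
| 0.8 | 0.5 | 38 | 63 | 69 | 79 |
| 0.8 | 0.7 | 52 | 77 | 89 | 92 |
| 1.0 | 0.5 | 22 | 40 | 50 | 60 |
| 1.0 | 0.7 | 32 | 52 | 72 | 77 |
| 1.2 | 0.5 | 14 | 25 | 37 | 46 |
| 1.2 | 0.7 | 20 | 33 | 56 | 62 |

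At s = 0.3 every method is at or near 100%. With 22 per arm the pattern is the same (s = 1.0: 28–40% planned, 73–87% log ANCOVA).

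**5. Where the loss comes from.** Share of the gap between the planned test and log ANCOVA that the baseline covariate closes on the raw scale:
- s = 0.6, ρ = 0.5: (91 − 65)/(96 − 65) = 84%
- s = 0.8, ρ = 0.7: (77 − 52)/(92 − 52) = 63%
- s = 1.0, ρ = 0.7: (52 − 32)/(77 − 32) = 44%
- s = 1.2, ρ = 0.5: (25 − 14)/(46 − 14) = 34%

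The split depends on which step is taken first: the log scale alone also closes much of the gap. Both contribute, and the scale matters more as skew grows.

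**6. A 30% reduction, planned test against log ANCOVA.** s = 0.3: 83–96% vs 97–99.6%. s = 0.5: 39–56% vs 63–79%. s = 0.8: 16–22% vs 31–42%. s = 1.0: 9–13% vs 21–29%. s = 1.2: 7–9% vs 16–21%.

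**7. Influence and Type I error, no effect.** The three most extreme of 34 patients supply a median 43% of the sum of squares of raw change at s = 0.3, 61–62% at 0.8 and 74–75% at 1.2, against 38% on the log scale. The planned test rejects in 3.2–5.1% of null trials.

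**The case against.** The strongest objection is that the skew is assumed. The protocol reports no distribution, SD or correlation for any of the three markers, and they need not share one spread. The entry criteria in section 7 require three months without infection or exacerbation and exclude collagen disease and malignancy, which may remove some extreme baseline values, though not extreme follow-up values. This stands. A reader might infer that a few high values will dominate and that a real effect will often be missed. The documents do not support that as a statement of fact, and for a halving it fails at a log-SD of 0.5 or below.

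A reader might also blame the measurement scale alone. Step 5 shows otherwise: at log-SD 0.6 and correlation 0.5, adding the baseline value on the raw scale does as well as taking logs without it (91% and 90%).

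Third, 17 per arm was set for SGRQ. For a 30% reduction at log-SD 0.8 or more, log ANCOVA also misses the effect in 58–84% of trials, so much of the weakness is sample size. This stands too, although the planned test still has lower power in each of those settings.

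Fourth, these are unpowered third-tier outcomes, and the t-test is a valid comparison of arithmetic mean change. A ratio of geometric means is a different quantity. This is correct, and it limits the severity.

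Finally, the plan says that "ratios or means of the differences between baseline and 12 weeks and between baseline and 52 weeks are calculated", which might be read as allowing a ratio analysis. The word is unexplained, more likely means proportions, and does not displace the t-test rule.

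**Conclusion.** The concern holds in conditional form and is minor. The protocol fixes an unadjusted raw-change t-test for three markers for which it expects a treatment effect. If they are right-skewed with proportional changes, that choice gives up power. Over log-SD 0.6 to 1.2 at correlation 0.5, with 17 per arm and a halving, power runs from 65% down to 14%, against 96% down to 46% for log-scale ANCOVA. At correlation 0.7 it runs from 82% down to 20%, against 99% down to 62%. Spread, correlation and effect size are all assumptions.

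The choice matters little for a halving at log-SD 0.5 or below, where the planned test already has at least 81% power. It does not rescue a 30% reduction at log-SD 0.8 or above. The harm is lost sensitivity, not false positives. A reader might infer that the trial's main result is weakened; it is not, because SGRQ has its own ANCOVA.

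**What to change.** In section 6, Statistical Analysis, exempt outcome C-j from the t-test rule. State that log concentration at 12 and at 52 weeks is compared by ANCOVA with log baseline and GOLD class as covariates, the same form of model as for the primary and secondary outcomes. Report the ratio of geometric means with its 95% CI, and describe the raw values by median and quartiles.

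The cost is a sentence or two in the protocol, with no new data, visits or patients. The downside is that results are expressed as ratios of geometric means instead of differences in arithmetic means, which some readers find less direct. If the markers turn out to have modest spread, little power is gained, but in the settings examined none is lost.

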## **B. Secondary outcome measures**

As for Secondary and other outcome measures, the following outcome were evaluated at baseline, 12 weeks, and one year (52 weeks) later.

- a: QOL questionnaire: SGRQ total domain difference 12 weeks after the baseline.
- b: QOL questionnaire: SGRQ domain other than Total domain (Symptom, Activity, Impact).
- c: The 6-minute walk test (6MWT) assesses dyspnea on exertion using the modified Borg Scale (Material D), walking distance, lowest oxygen saturation level, highest pulse count, and lower limb fatigue measured with the modified Borg Scale.

\*Evaluate the difference 12 weeks and one year (52 weeks) after the baseline.

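### The mixed model for SpO2 and pulse is aimed at the shift after week 12, not at the change from baseline at weeks 12 and 52 that the protocol asks for

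*Protocol*

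**What the plan says.** Three statements in the protocol bear on this.

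- **The question.** Section 6, Secondary outcome measures, item c, lists the walk-test variables, among them "lowest oxygen saturation level, highest pulse count". The note beneath them reads "Evaluate the difference 12 weeks and one year (52 weeks) after the baseline".
- **The general analysis.** Section 6, Statistical Analysis, item 2, says that "for main outcome measure and secondary outcome measures, we compare these 12-week-change and 52-week-change using the analysis of covariance (ANCOVA"), with baseline value and GOLD class as covariates and "treatment group as the factor of interest".
- **The separate rule.** Later in the same item comes a rule that opens "For the changes in arterial blood oxygen saturation and in pulse during the 6-minute walk" and continues "we use the mixed effects model to analyze the difference between the 12-week-change and 52-week change". In that model "the fixed effects are groups and times, the interaction terms are group x time", and "the intercept of random effects is individual, the slope is time, and the estimation method is the maximum likelihood method".

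The separate rule leaves four things unstated: whether the response is the two changes or the three visit values, whether time is categorical or linear, which term carries the result, and whether the model replaces or supplements the ANCOVA.

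**The concern.** The mixed-model sentence does more than leave detail open. It states a target, and that target differs from the question set for the same test. The difference between the two changes says whether a patient moved between week 12 and week 52. It does not say whether the patient differs from baseline at either visit.

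This matters because of the trial's purpose. Section 5 argues that a short-term effect has been shown and that the long-term effect is now to be evaluated. The hoped-for result is an effect present by week 12 and still present at week 52. On the stated target such an effect is zero, so the mixed model could report nothing where there is something. An early effect that has disappeared by week 52 would give a non-zero result, which could be misread as evidence of a year-long effect.

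**Working it through.** **1. The target, algebraically.**

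(week 52 − baseline) − (week 12 − baseline) = week 52 − week 12.

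Baseline drops out. Let δ12 and δ52 be the between-group differences in change from baseline. The group x time contrast on the two changes is then δ52 − δ12. If δ52 = δ12 it is zero, and the test rejects at its alpha level whatever the effect size or correlation.

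**2. Inputs.** From the Sample Size section: two-sided alpha 0.05, 17 evaluable patients per group, and a standardised effect of 10/10 = 1 SD of change. That effect is borrowed from the SGRQ calculation, because the protocol gives none for SpO2 or pulse. The correlation ρ between the two change scores is not given; I assume 0.3 to 0.7, with equal SDs at both visits.

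**3. The plan's own figure.** The noncentral t-test has noncentrality d·√(n/2). With d = 1 and n = 17 this is √8.5 = 2.915 on 32 df, and power is 0.807; with n = 16 it is 0.781. So 17 per group reproduces. The same 0.807 is the power of the group contrast in 52-week change for a 1-SD effect.

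**4. Literal reading: two changes as response, group x time as the test.** In balanced data this is a two-sample t-test on the difference of the changes, with SD √(2(1 − ρ)).

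- *Sustained effect (δ12 = δ52 = 1):* noncentrality 0, so rejection is 5%. Simulation gave 4.8–5.2%. A separate check with 300 maximum-likelihood fits gave 9% (simulation error about 1.7 points); some excess over 5% is expected from a normal reference distribution with 34 patients.
- *Effect lost by week 52 (δ12 = 1, δ52 = 0):* standardised effect 1/√(2(1 − ρ)).

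| ρ | Standardised effect | Noncentrality | Rejection |
|---|---|---|---|
| 0.3 | 0.845 | 2.464 | 67% |
| 0.5 | 1.000 | 2.915 | 81% |
| 0.7 | 1.291 | 3.764 | 95% |

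The week-52 group contrast rejects in 5% of trials in that second scenario, as it should.

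**5. Three visits, linear time in weeks (compound symmetry).** Centred times are −21.33, −9.33 and 30.67, with sum of squares 1482.67. A change SD of 1 implies a within-patient variance of 0.5, so the SD of a patient's slope is √(0.5/1482.67) = 0.01836.

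- *Sustained:* slope difference (−9.33 + 30.67)/1482.67 = 0.01439; standardised 0.784; noncentrality 2.284; power 60%.
- *Lost by week 52:* slope difference −9.33/1482.67 = −0.00629; standardised 0.343 in size; noncentrality 0.999; rejection 16%.

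**6. Other readings that the text allows, sustained effect.**

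- Joint 2-df group x time test with baseline as a categorical visit: 83%.
- Group main effect on the two changes: the SD of their mean is √((1 + ρ)/2), giving noncentralities of 3.616, 3.367 and 3.162 and power of 94%, 90% and 87% at ρ = 0.3, 0.5 and 0.7.

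One sentence therefore allows anything from 5% to about 94% for the same true effect.

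**The case against.** The case on the other side is strong on several points.

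- **The ANCOVA appears to cover these variables.** Lowest SpO2 and highest pulse are secondary outcomes, and the ANCOVA rule makes no exception for them. This stands. A reader might infer that the plan as a whole would miss a sustained effect on SpO2 and pulse; the documents do not support that.
- **No term is named as decisive.** Group is also a fixed effect. A reader might infer that the model can detect a sustained effect only at the alpha rate; that holds only if the response is the two changes and group x time is the test.
- **The random effects fit the two-change reading poorly.** With two responses per patient, a random intercept, a random time slope and a residual variance cannot all be identified. This points towards three visits in the model, where power is 60% or 83% depending on time coding. It stands as an argument against the literal reading, though the stated target still belongs to that reading.
- **The wording may simply be loose.** The ANCOVA sentence is phrased in much the same way. But it goes on to name treatment group as the factor of interest, which settles its meaning; the mixed-model sentence has nothing equivalent.
- **The model may describe the course within the walk** rather than the single lowest and highest values. The text leaves this open. The stated target would still be the shift after week 12.
- **Such detail belongs in a statistical analysis plan.** That is fair for time coding and the tested term. It does not answer a target that the protocol states and that differs from its own question.

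**Conclusion.** The concern holds in limited form. The protocol states a contrast for SpO2 and pulse that does not match the change from baseline at weeks 12 and 52 set as the question.

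The size of the harm depends on the reading. It is greatest on the literal one (5% against about 81% for a sustained effect) and moderate with linear time over three visits (60% against 81%, with a vanished effect flagged in about 16% of trials). It is absent for a sustained effect if the joint categorical-time test or the group main effect is used.

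The 5% follows from algebra alone. The other figures rest on 17 per group, a 1-SD effect borrowed from SGRQ, equal SDs and, where it enters, an assumed correlation. The concern is confined to the mixed-model result for two walk-test variables; the SGRQ primary analysis is unaffected. The correction is worth making because it costs almost nothing.

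**What to change.** Replace the target sentence with wording such as: *For SpO2 and pulse, the mixed model has visit as a categorical factor with group x visit terms. The reported contrasts are the between-group differences in change from baseline at week 52 (main) and at week 12, each with a 95% confidence interval. The group x visit interaction is reported only to describe whether the effect differs between visits.*

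Alternatively, state that the ANCOVA already specified for secondary outcomes governs for these two variables. If the mixed model is kept beside the ANCOVA, say which result takes precedence. If it is meant for the course within the walk, say so.

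The cost is one sentence of wording and no new data. The small downside is that the interaction is no longer the headline result of that model.

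### The mixed model for SpO2 and pulse in the 6-minute walk is fixed at maximum likelihood without GOLD stage, and its response, time scale and relation to the ANCOVA rule need settling

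*Protocol*

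**What the plan says.** Four statements in section 6 of the Protocol bear on this.

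- Statistical Analysis, item 2, gives a general rule: 12-week and 52-week changes in the main and secondary outcomes are compared "using the analysis of covariance (ANCOVA) with baseline values and GOLD classification as covariates and treatment group as the factor of interest".
- The same item then gives a specific rule: "For the changes in arterial blood oxygen saturation and in pulse during the 6-minute walk, we use the mixed effects model" and the aim is "to analyze the difference between the 12-week-change and 52-week change". Its terms are spelled out: "the fixed effects are groups and times, the interaction terms are group x time", and "the intercept of random effects is individual, the slope is time, and the estimation method is the maximum likelihood method". Neither GOLD stage nor a baseline value is listed.
- Secondary outcome measures, item c, lists among the walk-test outcomes "walking distance, lowest oxygen saturation level, highest pulse count, and lower limb fatigue measured with the modified Borg Scale". The section says that "the following outcome were evaluated at baseline, 12 weeks, and one year (52 weeks) later".
- Random allocation makes GOLD stage (II, III or IV) the stratification factor.

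**The concern.** The Protocol does not leave this model open: it names the fixed effects, the random effects and the estimator. Three things then look wrong.

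1. ML makes no allowance for the fixed effects when it estimates variances, so standard errors come out too small in a small trial.
2. GOLD stage is used in the design and in the ANCOVA, but is absent here without a stated reason.
3. The response could be two change scores, three visit values or serial readings within the walk. The listed terms do not suit each of these equally, and on some readings the same outcomes also fall under the ANCOVA rule.

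At stake are slightly small p-values, some lost precision, and room to choose between two analyses of lowest SpO2 and highest pulse once the results are known.

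**Working it through.** **Inputs.** Sample Size gives 17 per group (34 in total), a target of 44 and 10 expected dropouts, so 44 − 10 = 34 patients analysed when dropouts are excluded. The Protocol gives no figure for the mixed model. Its 17 per group reproduces with a two-sided t test (difference 10, SD 10, alpha 0.05): power is 0.807 at 17 per group and 0.781 at 16.

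**1. ML against REML.** Take a two-group contrast with complete balanced data and saturated mean and covariance. ML divides by N and REML by N − 2, so the ratio of standard errors is √((N − 2)/N). Type I error with a normal reference is P(|t| > 1.96·√((N − 2)/N)) for ML and P(|t| > 1.96) for REML, with t on N − 2 degrees of freedom.

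| | N = 34 | N = 44 |
|---|---|---|
| SE ratio, ML/REML | √(32/34) = 0.970 | √(42/44) = 0.977 |
| ML, normal reference | 0.066 | 0.062 |
| REML, normal reference | 0.059 | 0.057 |
| ML, t reference | 0.057 | 0.055 |
| REML, t reference | 0.050 | 0.050 |

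ML therefore lowers the standard error by 3.0% at N=34 and 2.3% at N=44.

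A null simulation with assumed components (intercept SD 0.8, slope SD 0.4, residual SD 0.6; 1000-1200 runs per setting) agrees on the standard errors. At N=34 the means are 0.310 (ML) and 0.320 (REML) for two change scores, and 0.314 and 0.323 for three visits. Simulated ML type I error with a normal reference ran from 0.057 to 0.073. The Monte Carlo error of about 0.007 is as large as the gap between ML and REML.

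**2. Response is the two change scores.** Let a be the intercept variance, b the slope variance, c their covariance and s² the residual variance. With time coded 0 and 1, the three distinct covariance elements are:

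- Var₁ = a + s²
- Cov = a + c
- Var₂ = a + 2c + b + s²

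If c = 0, there are three equations for three unknowns: a = Cov, s² = Var₁ − Cov, b = Var₂ − Var₁. The model is just identified. If c is free, there are four unknowns at rank 3, and it is not identified.

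**3. Response is the three visit values.** There are six covariance elements, and four parameters at rank 4, so the model is identified. Baseline enters through the response. GOLD is still absent.

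**4. Response is serial readings within the walk.** With an assumed seven readings there are 28 elements, and four parameters at rank 4, so the model is again identified. But group, time and group × time, with time meaning time within the walk, contain no visit effect. One such model cannot estimate a contrast between the 12-week and 52-week changes.

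**5. Overlap with the ANCOVA rule.** The secondary outcomes are one saturation value and one pulse value per test, the lowest and the highest. The mixed-model sentence speaks of changes during the walk. If these are the same variables, both rules apply and neither is given precedence. If they are courses over the walk, they are different variables and the two rules do not collide.

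**The case against.** The best defence is that the mixed model describes the course of saturation and pulse over the walk, while the ANCOVA handles the nadir and the peak. A random time slope suits that reading, and even if the variables are the same, a specific sentence can be read as an exception to a general one. The wording about comparing the two changes is loose in the ANCOVA sentence too, so the model might be meant for each change separately, with no visit term needed. Covariance structure and degrees-of-freedom method are ordinary SAP content, so their absence here is no fault. All of this is fair, and it makes points 2, 4 and 5 of the working conditional.

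Several stronger conclusions are tempting but unsupported:

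- *The model is over-parameterised.* Non-identification needs both a two-change-score response and correlated random effects, and the Protocol states neither. Nothing calculated here shows that convergence failure is likely.
- *ML by itself causes a 6.6% error rate.* That figure joins ML to an assumed normal reference. REML with the same reference still gives 5.9% at N=34.
- *Baseline is omitted.* It is not, if visit values form the response.
- *Leaving out GOLD inflates false positives.* In a stratified randomised comparison the cost is precision, and the test tends to be conservative.
- *The two rules flatly contradict each other.* They do so only if the variables are the same.

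What the defence does not answer is that the Protocol itself chose ML for about 34 patients and listed terms that exclude GOLD.

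**Conclusion.** The point holds in a limited form. On every reading, ML is specified and GOLD is missing. ML lowers standard errors by 2-3% at N=34-44. The resulting type I error of about 6.6% (N=34) or 6.2% (N=44) rests on a normal reference and on the balanced two-group case, not on the random-slope model itself.

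The identification problem, the missing visit term and the overlap with the ANCOVA are each real on one reading of the text and absent on another, so they call for clarification and are not demonstrated errors. Two of the walk-test secondary outcomes are at most affected, and the SGRQ primary analysis is untouched.

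**What to change.** - Fit by REML with Kenward-Roger degrees of freedom.
- Add GOLD stage as a fixed effect, and the baseline value if the response is a change.
- State the response. If it is the week-12 and week-52 changes, replace the random slope with an unstructured 2×2 covariance. If it is serial readings within the walk, keep the random slope and add visit with its interactions with group and time.
- Name the ANCOVA as governing for lowest SpO2 and highest pulse, with the mixed model supportive.

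The cost is a few sentences and a respecified model. In the balanced case REML raises standard errors by 1/0.970 − 1 = 3.1% at N=34 and 1/0.977 − 1 = 2.4% at N=44, so p-values rise slightly. GOLD, with three strata, uses two further parameters.
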